### Safety assessment

The experiment will ask subjects to report adverse events (AEs), such as unexpected physical changes or side effects, in person when they visit and/or by telephone at other times during the study.

Every adverse event reported by subjects will be described in the case report form (CRF). If the adverse event is severe and associated with the trial, the participant will be withdrawn from the study and given appropriate medical care.

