On the second visit day for the baseline evaluation and the first treatment, all patients will also complete the PSQI, ISI, BDI, STAI, K-AVLT, and the DS, with HRV measured at baseline (prior to first treatment), after the last treatment, and at the 1-week follow-up. EEG recordings will be used as objective measures to validate self-reported insomnia symptoms. ERPs will be measured at baseline and after the last treatment using an odd-ball task. Spontaneous EEGs will also be measured at baseline after the last treatment for spectral analysis. All subjects will complete the WHOQOL-BREF at baseline and at 1-week follow-up. They will also complete the Temperament Character Inventory (TCI) at baseline. All patients will also complete a sleep log every day from baseline to the 1-week follow-up [27]. The Credibility of Treatment Rating Scale (CTRS) will be administered to assess the maintenance of blind conditions after the second treatment [28].

Registered patients shall be randomly divided into the experimental and sham control groups, with an equal number of patients assigned to each group. Patients will then complete either the experimental or sham acupuncture treatment 3 times, with 2- to 3-day intervals, within 1 week.

Figure 1 is an overview of this trial, and Figure 2 is an approximate visit schedule.

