### Outcomes

#### Primary outcome

The primary outcome of this study will be the changes in the ISI between the baseline, post-treatment assessment, and 1-week follow-up.

The PSQI is an effective self-report questionnaire used to assess the quality of sleep and sleep disturbances. The PSQI is comprised of 19 items consisting of the following components: subjective sleep quality, sleep latency, sleep duration, habitual sleep efficiency, sleep disturbances, use of sleeping medication, and daytime dysfunction. The ISI is a five-point Likert-scale self-rate questionnaire designed to assess the nature, severity, and impact of insomnia, and is widely used to measure responses to treatment in research studies and clinical trials.

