### Sample size

Sample size was calculated based on a ratio of 1:1 between the experimental and control groups. This sample size is based on a study that investigated the effect of acupuncture treatment on insomnia using ISI as a primary outcome [30]. In that study, the mean change in ISI between the experimental and control groups was 3.8 and the standard deviation was estimated as the median between the experimental (SD =4.0) and control groups (SD =3.2). Based on a two-tailed alpha error of 5% and with a statistical power of 80%, the calculated sample size is based on the equation:

Therefore, all 38 participants will be randomly assigned with 19 subjects in each group, assuming a 20% dropout rate.

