### Randomization

An expert will randomly generate a block size (4 or 6) sequence using Microsoft Excel (Redmond, WA, USA). After that, with the allocation ratio of the experimental and control group within each block kept at 1:1, the expert will randomly generate the numbers 0 (control group) or 1 (experimental group) through Microsoft Excel. This expert will not contact any of the patients during the experiment. Once the expert generates the random numbers, the expert will seal each number in an opaque envelope. The expert lets the clinician know each random number as the clinician calls a patient by telephone. Two other experts (neuropsychologists) - who measure the self-reported tests, the psychological (cognitive) tests, the EEG and HRV - will be blinded. Only the clinician who treats acupuncture therapy knows what treatment the patient has been administered, but he is prohibited from accessing any measurements for outcomes. Double-blinding is almost impossible due to the specifications of the acupuncture treatment. Thus, in this trial, only the neuropsychologist (assessor), the statistical expert, and patients will be blinded.

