### Statistical method

The primary outcome variable for efficacy analysis is ISI, and secondary outcomes are the PSQI, BDI, STAI, WHOQOL-BREF, sleep logs, K-AVLT, DS, EEG, and HRV. Demographics, sleep logs, ISI, PSQI, K-AVLT, Digit Span, STAI, TCI, EEG, and HRV will be analyzed using independent sample *t*-tests at baseline to determine equality of the two groups. A chi-square test will be used to assess sex differences. An efficacy analysis will be done using both per-protocol and intention-to-treat analyses.

Independent *t*-tests between the two groups and a repeated-measures analysis of variance (ANOVA) will be used to determine and compare the effect of acupuncture. The factors are treatment (3 levels: pre-, post-acupuncture and 1-week follow-up) and groups (2 levels: treatment and sham) and their interaction. The significance level was set at *P <*0.05 and *post-hoc* analyses were performed where appropriate.

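### The adverse-event rule withdraws the patient from the study, not only from treatment, so the promised intention-to-treat analysis may lose post-baseline ISI scores for informative reasons

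*Protocol article*

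**What the plan says.** The Safety assessment section sets the rule: "If the adverse event is severe and associated with the trial, the participant will be withdrawn from the study". The sentence then provides for medical care. It refers to the study, not to study treatment, and no other section mentions outcome assessment after such a withdrawal.

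The Statistical method section commits to two analysis sets: "An efficacy analysis will be done using both per-protocol and intention-to-treat analyses".

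The outcome at stake is the ISI. The Primary outcome section reads: "The primary outcome of this study will be the changes in the ISI between the baseline, post-treatment assessment, and 1-week follow-up". The Setting section places all treatment before the first post-baseline score: "Patients will then complete either the experimental or sham acupuncture treatment 3 times, with 2- to 3-day intervals, within 1 week".

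The Sample size section allows for 20% dropout and randomises 19 patients per arm.

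**The concern.** Intention-to-treat analysis is meant to compare the arms as randomised, whatever happened to treatment. It does that best when outcomes are still collected from patients who stop treatment. A rule that ends study participation after a related adverse event works against this, because it ends collection for patients picked out by something that happened to them in the trial. An analysis method applied later can only make assumptions about scores that were not collected.

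At stake is the ISI comparison. If the withdrawn patients would have changed differently from the rest, and if there are more of them in one arm, the estimated difference is biased. The dropout allowance offers no protection: it replaces lost numbers but does not correct for who was lost.

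This is a point about what data are collected. How the analysis treats a missing visit is a separate matter, which may be covered in a statistical analysis plan or full protocol that is not shown, and it is not counted here.

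**Working it through.** **1. The plan's own sample size.** Inputs from the Sample size section: difference 3.8, SD 3.6 (midpoint of 4.0 and 3.2), two-sided alpha 5%, power 80%, ratio 1:1, dropout 20%.

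n per arm = 2 × [SD × (z for alpha + z for power) / difference]² = 2 × [3.6 × (1.960 + 0.842) / 3.8]² = 14.09, rounded up to 15. Then 15 / (1 − 0.20) = 18.75, rounded up to 19 per arm, 38 in total. The stated figure reproduces and is not in dispute. The allowance is therefore 19 − 15 = 4 patients per arm, a count with no reference to why they leave.

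**2. Which scores a literal reading removes.** From the Setting, Primary outcome and Safety assessment sections:

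| Time of event | ISI kept | ISI lost |
|---|---|---|
| During the treatment week | baseline | post-treatment and 1-week follow-up |
| After the post-treatment assessment | baseline and post-treatment | 1-week follow-up |

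In the first row the patient has no post-baseline ISI. Such a patient is still randomised, but brings no observed change to the intention-to-treat comparison.

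**3. Illustrative size.** Two assumptions, neither given in the documents: k of the 19 patients in one arm are withdrawn and none in the other, and their unobserved ISI change is g points worse than that of the completers in their arm.

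Let m be the completers' mean. The full-arm mean is [(19 − k) × m + k × (m + g)] / 19 = m + k × g / 19. Using completers alone therefore shifts the arm mean, and the arm difference, by k × g / 19.

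| k | g = 2 | g = 7 | As a share of 3.8 |
|---|---|---|---|
| 1 | 1 × 2 / 19 = 0.11 | 1 × 7 / 19 = 0.37 | 2.8% to 9.7% |
| 2 | 2 × 2 / 19 = 0.21 | 2 × 7 / 19 = 0.74 | 5.5% to 19.4% |

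The formula holds for a gap measured against completers. For a gap measured against the full-arm mean the divisor is 19 − k, which is slightly larger in effect: 2/18 to 7/18 = 0.11 to 0.39 for one patient, and 4/17 to 14/17 = 0.24 to 0.82 for two.

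**4. Direction and cancellation.** Withdrawals in the experimental arm under these assumptions flatter acupuncture; withdrawals in the sham arm do the opposite. If both arms lose k patients with the same g, the shift is k × g / 19 − k × g / 19 = 0.

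**The case against.** The strongest reply is that the two sections can both be followed as written. Intention-to-treat fixes the group in which a patient is analysed, and it can be carried out with some outcomes missing. The Sample size section already expects dropout alongside it. A reader might infer a flat contradiction between the safety rule and the analysis; the documents do not support that. It is also fair to say that a journal article condenses, and that the sentence does not say in terms that assessment stops. What remains is that the rule is stated, that its wording reaches the whole study, and that staff following it literally would stop assessing.

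Three other stronger readings are tempting and also go beyond the text:

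- **That the lost patients are those who did worst.** No section links adverse events to ISI, and a severe reaction to needling is not the same as a poor sleep response. The event need not come from the needles either, since the wording covers association with the trial as a whole. The gap g is purely an assumption.
- **That the arms will lose different numbers.** Under Interventions and Table 1, both arms receive five needles for 20 minutes and then intradermal needles for 48 to 72 hours. They differ only in point location and in whether the de-qi sensation is sought. Equal event rates are not guaranteed, but unequal rates are only a possibility. The trigger is narrow (severe and related), and no rate is given.
- **That the unblinded acupuncturist decides relatedness.** The Randomization section says "Only the clinician who treats acupuncture therapy knows what treatment the patient has been administered", but no section says who judges whether an event is related. The point does not depend on this.

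**Conclusion.** The point holds as a weakness in the data-collection rule. Taken literally, that rule ends ISI collection after a severe, trial-related event, and the loss may be informative for the promised intention-to-treat analysis. Its size is unknown and possibly small. On the assumptions above (all withdrawals in one arm, change 2 to 7 points worse than completers), the shift is 0.11 to 0.37 ISI points for one patient and 0.21 to 0.74 for two, against a planned 3.8. With similar losses in both arms it would largely cancel. No figure in the plan is wrong, and the sample size is unaffected. This is a cheap improvement, not an error that undermines the trial.

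**What to change.** Leave the clinical decision and the medical care in the Safety assessment section as written. Reconcile that section with Statistical method by adding that, for such a patient, ISI and PSQI are still collected at post-treatment and at 1-week follow-up, by phone or post if needed, unless the patient withdraws consent. State that these values enter the intention-to-treat analysis.

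Both questionnaires are self-report, the Safety assessment section already uses telephone contact for adverse events, and the trial lasts 18 days, so the burden is light. The cost is one sentence in the protocol and consent text and a few extra questionnaires. The total stays at 38.

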### Sample size

Sample size was calculated based on a ratio of 1:1 between the experimental and control groups. This sample size is based on a study that investigated the effect of acupuncture treatment on insomnia using ISI as a primary outcome [30]. In that study, the mean change in ISI between the experimental and control groups was 3.8 and the standard deviation was estimated as the median between the experimental (SD =4.0) and control groups (SD =3.2). Based on a two-tailed alpha error of 5% and with a statistical power of 80%, the calculated sample size is based on the equation:

Therefore, all 38 participants will be randomly assigned with 19 subjects in each group, assuming a 20% dropout rate.

### Randomization

An expert will randomly generate a block size (4 or 6) sequence using Microsoft Excel (Redmond, WA, USA). After that, with the allocation ratio of the experimental and control group within each block kept at 1:1, the expert will randomly generate the numbers 0 (control group) or 1 (experimental group) through Microsoft Excel. This expert will not contact any of the patients during the experiment. Once the expert generates the random numbers, the expert will seal each number in an opaque envelope. The expert lets the clinician know each random number as the clinician calls a patient by telephone. Two other experts (neuropsychologists) - who measure the self-reported tests, the psychological (cognitive) tests, the EEG and HRV - will be blinded. Only the clinician who treats acupuncture therapy knows what treatment the patient has been administered, but he is prohibited from accessing any measurements for outcomes. Double-blinding is almost impossible due to the specifications of the acupuncture treatment. Thus, in this trial, only the neuropsychologist (assessor), the statistical expert, and patients will be blinded.

### Statistical method

The primary outcome variable for efficacy analysis is ISI, and secondary outcomes are the PSQI, BDI, STAI, WHOQOL-BREF, sleep logs, K-AVLT, DS, EEG, and HRV. Demographics, sleep logs, ISI, PSQI, K-AVLT, Digit Span, STAI, TCI, EEG, and HRV will be analyzed using independent sample *t*-tests at baseline to determine equality of the two groups. A chi-square test will be used to assess sex differences. An efficacy analysis will be done using both per-protocol and intention-to-treat analyses.

Independent *t*-tests between the two groups and a repeated-measures analysis of variance (ANOVA) will be used to determine and compare the effect of acupuncture. The factors are treatment (3 levels: pre-, post-acupuncture and 1-week follow-up) and groups (2 levels: treatment and sham) and their interaction. The significance level was set at *P <*0.05 and *post-hoc* analyses were performed where appropriate.

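### The promised intention-to-treat analysis is paired with a repeated-measures ANOVA that, without imputation, would drop about 8 of the 38 patients at the planned dropout

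*Protocol article*

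**What the plan says.** All of the following is in the protocol article.

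- **Analysis sets** (Statistical method): "An efficacy analysis will be done using both per-protocol and intention-to-treat analyses". Neither set is defined further.
- **Model** (Statistical method): independent t-tests between the groups, and "a repeated-measures analysis of variance (ANOVA) will be used to determine and compare the effect of acupuncture". The structure is fixed: "The factors are treatment (3 levels: pre-, post-acupuncture and 1-week follow-up) and groups (2 levels: treatment and sham) and their interaction".
- **Primary outcome** (Primary outcome): "The primary outcome of this study will be the changes in the ISI between the baseline, post-treatment assessment, and 1-week follow-up", so the same three visits as the model.
- **Sample size** (Sample size): "all 38 participants will be randomly assigned with 19 subjects in each group", "assuming a 20% dropout rate".
- **Withdrawal** (Safety assessment): after an adverse event that is both severe and trial-related, "the participant will be withdrawn from the study and given appropriate medical care".

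The article gives no rule for a missing ISI visit. It does not say that patients with a missing visit are excluded from either analysis.

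**The concern.** Intention-to-treat means that all randomized patients are analysed in the arm to which they were assigned. A classical repeated-measures ANOVA takes one complete row per patient and deletes the whole row if any visit is missing. The promise and the named model are therefore compatible only if values are imputed beforehand.

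Three things are at stake.

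- A patient seen post-treatment but missed at follow-up would lose a score that was already collected.
- The t-tests and the ANOVA, named together as the efficacy analysis, could rest on different patients at the same visit.
- If patients leave for outcome-related reasons that differ between arms, a comparison of completers is biased, although the data to reduce that bias are in hand.

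The Safety assessment wording adds a smaller problem. Read literally, leaving the study ends outcome collection as well as treatment, and no later analysis can recover scores that were never requested.

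**Working it through.** **Inputs from the Sample size section.** Difference 3.8 ISI points; SDs 4.0 and 3.2, midpoint 3.6; two-sided alpha 5%; power 80%; dropout 20%; 19 per arm.

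**1. The plan's own figure.** n per arm = 2 × (3.6 × (1.960 + 0.842) / 3.8)² = 14.09, rounded up to 15. Allowing for dropout, 15 / 0.8 = 18.75, rounded up to 19 per arm, 38 in total. This matches the article.

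**2. Patients left in a complete-case ANOVA.** 38 × 0.8 = 30.4, so about 30 remain and about 8 are lost. This takes each dropout to miss at least one ISI visit.

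**3. Power.** For 3.8 points and SD 3.6, 15 per arm gives 82% (normal) or 80% (t); all 19 per arm gives 90% or 89%. The loss was already paid for in the sample size.

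**4. Possible bias at follow-up.** The article gives neither the correlation between visits nor a dropout mechanism, so these are assumptions. In 4,000 simulated trials per case there were 19 per arm, changes with SD 3.6, and correlation 0.6 between the post-treatment and follow-up changes. About 20% were lost, all after the post-treatment visit. Where selective, dropout followed a logistic function of the standardized post-treatment change (slope 1.5). The completers' comparison was a t-test on follow-up change, standing in for the ANOVA. The likelihood analysis was represented by regression on the post-treatment change. Estimates are sham minus active, so positive favours acupuncture.

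| Dropout mechanism | Completers, true 0 (rejection rate) | Completers, true 3.8 (rejection rate) | All visits, true 0 / 3.8 |
|---|---|---|---|
| Random | 0.00 (5.6%) | 3.81 (80.5%) | 0.01 / 3.81 |
| Same selection in both arms | 0.02 (5.1%) | 3.82 (82.6%) | 0.01 / 3.83 |
| Poor responders leave sham; active at random | -0.46 (5.9%) | 3.29 (68.9%) | 0.05 / 3.79 |
| Poor responders leave active; good responders leave sham | 1.02 (11.6%) | 4.84 (95.4%) | 0.01 / 3.83 |

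The post-treatment comparison on all observed scores, as a t-test at that visit would make it, stayed within 0.03 of the truth in every case.

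**5. Sensitivity to the correlation.** A large-sample run at correlation 0.5 with outcome-driven loss in sham only gave a follow-up bias of 0.44 points with 20% lost in each arm, and 0.64 with 30% lost in sham and 10% in active. In the same runs the completers' bias at post-treatment was 0.90 and 1.27 points. That bias comes only from discarding scores already collected.

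A closed-form ceiling for the 20% case: if the worst 20% of sham left with certainty, the sham mean would shift by 3.6 × 0.280 / 0.8 = 1.26 points at post-treatment. At follow-up the shift would be 1.26 × 0.5 = 0.63, or 1.26 × 0.6 = 0.76. The simulated 0.44 and 0.46 lie below these.

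**The case against.** The strongest reply is that the article nowhere states complete-case handling. Imputing before the ANOVA would keep all 38 patients and contradicts nothing in the text. Missing-data rules are commonly left to the analysis plan or full protocol, which are not shown. This stands, and it limits the point: the absence of an imputation rule is not the finding. What remains is that the article fixes a model which cannot deliver the promised analysis without such a step, when a model that can is readily available.

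Second, the t-tests in the same sentence do not need all three visits, so a patient lost after the post-treatment assessment can still count there. This is also right. The post-treatment biases above apply to the ANOVA, not to such a t-test. It does not repair the ANOVA, and it leaves two named analyses resting on different patients.

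Third, nothing in the article suggests that dropout would differ by arm. Patients and assessors are blinded, the procedures are the same apart from point location and the needling sensation sought, and the trial lasts 18 days. The 20% is a planning allowance. The withdrawal rule covers only events that are both severe and trial-related, and no rate is given. All of this bears on how likely bias is.

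A reader might also infer that the intention-to-treat and per-protocol sets would nearly coincide. The article defines neither, and a per-protocol set could also exclude completers who missed sessions, so that inference is not supported.

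**Conclusion.** The point holds in conditional form. Unless missing ISI values are filled in first, the named ANOVA would analyse about 30 of 38 patients at the assumed dropout and discard observed post-treatment scores. It is tempting to conclude that the intention-to-treat result will be a biased completers-only result. The article supports neither half of that: exclusion is an inference from the model, and 20% dropout alone does not create bias.

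Bias needs dropout that relates to outcome differently in the two arms. Under the assumed mechanisms it runs from about 0 to about 1 ISI point at follow-up, against a 3.8-point target. If poor responders leave sham only, the bias works against acupuncture: a true 3.8 becomes about 3.3. Only opposing selection in the two arms inflated the type I error materially, to about 12%. These sizes rest on SD 3.6, correlations of 0.5 to 0.6 and dropout after the post-treatment visit; the correlations and the timing are not in the article.

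The sample size and its power, near 80%, are not affected. This is a change that should be made, not one on which the trial's validity turns.

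**What to change.** **Analysis.** For ISI, replace the repeated-measures ANOVA with a likelihood-based mixed model with visit, group and group-by-visit terms, an unstructured covariance and small-sample degrees of freedom (for example Kenward-Roger). Fit it to all available visits of all randomized patients, as randomized. One suitable form includes baseline ISI as a response with its mean constrained equal between arms. This also keeps patients lost before the post-treatment visit, whom a model with baseline as covariate would leave out. The approach assumes that dropout depends only on observed data. In the simulated cases of that kind its residual bias was below about 0.05 points.

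**Data collection.** Reconcile the withdrawal wording in Safety assessment with the intention-to-treat promise in Statistical method. Record the end of treatment separately from the end of data collection, and still request ISI at the remaining visits where the patient agrees. The clinical criterion for withdrawal is not at issue.

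**Cost.** Revised analysis wording, one added line on the case report form, slightly more analysis work, and a few extra questionnaires by telephone or post. The number randomized stays at 38.

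### No decisive ISI test is named: unranked t-tests and a repeated-measures ANOVA, two visits and two analysis sets, all at P<0.05, in a trial sized for one comparison

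*Protocol article*

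**What the plan says.** All references are to the protocol article.

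- **Hypothesis:** symptoms are relieved more in the acupuncture group than in the sham group, which is a between-group statement.
- **Primary outcome:** "changes in the ISI between the baseline, post-treatment assessment, and 1-week follow-up". This gives two post-baseline visits, and neither is called primary.
- **Statistical method, variable:** "The primary outcome variable for efficacy analysis is ISI".
- **Statistical method, tests:** "Independent *t*-tests between the two groups and a repeated-measures analysis of variance (ANOVA) will be used to determine and compare the effect of acupuncture". The ANOVA has a within-patient factor, labelled as treatment, whose three levels are the three assessment times. It also has "groups (2 levels: treatment and sham) and their interaction".
- **Statistical method, analysis sets:** "An efficacy analysis will be done using both per-protocol and intention-to-treat analyses".
- **Statistical method, level:** "The significance level was set at *P <*0.05 and *post-hoc* analyses were performed where appropriate".
- **Sample size:** one two-group comparison of ISI change. "Based on a two-tailed alpha error of 5% and with a statistical power of 80" (per cent).

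**The concern.** The hypothesis is one between-group question, and the sample size answers one such question at 5%. The Statistical method section offers several routes to an answer: a t-test at either visit (on scores or on changes), the interaction, and the group main effect, each in two analysis sets. These can disagree, and the text does not say which one settles the matter. If the choice is made after the data are seen, the nominal 5% no longer describes the error rate of the ISI claim.

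The ANOVA labelling adds a second problem. A main effect of the factor called treatment is the average change from before to after treatment across both arms. It would be significant if acupuncture and sham improved equally, and the Discussion itself accepts that sham may lead to improvement. The first objective, which speaks of examining significant improvement without mentioning the comparison, makes that misreading easier.

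**Working it through.** **1. The design figure reproduces.** Inputs from Sample size: difference 3.8; SD midway between 4.0 and 3.2, so 3.6; two-sided 5%; power 80%; dropout 20%.

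n per arm = 2 × (1.960 + 0.842)² × 3.6² / 3.8² = 14.09, rounded up to 15. With dropout, 15 / 0.80 = 18.75, rounded up to 19 per arm, 38 in total. The stated N is correct, and it is the N for one two-group comparison.

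**2. What the document does not fix.** It gives no correlation between visits, no choice between visit scores and change scores for the t-tests, and no success rule. Any error rate therefore needs assumptions.

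**3. Null simulation, one analysis set.** Assumptions: no group difference, SD 3.6, equal correlation of 0.3 to 0.7 between the three visits, 15 or 19 per arm, 20,000 replicates per scenario. Each entry is the chance of at least one P<0.05 among the tests listed.

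| Tests that count as success | Chance |
|---|---|
| Interaction alone | about 5% |
| Change-score t-tests at two visits | about 9% |
| Same, plus interaction | about 10% |
| Visit-score t-tests at two visits | 8-10% |
| Same, plus interaction | 12-13% |
| Same, plus interaction and group main effect | 13-15% |

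The change-score rows hardly depend on the correlation ρ. Each change has variance 2σ²(1−ρ), and two changes from the same baseline have covariance σ²(1−ρ), so their correlation is 0.5 whatever ρ is.

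**4. Wider assumptions.** 19 per arm, correlations 0.3 to 0.9, dropout 5% or 20%, last value carried forward in intention-to-treat, completers as per-protocol, Greenhouse-Geisser correction, 40,000 replicates.

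| Tests that count as success | Chance |
|---|---|
| Change-score t-tests at two visits, one set | 6.8-9.2% |
| Same plus interaction, either set | 8.4-12.2% |
| Visit-score t-tests plus interaction, one set | 10.8-12.5% |
| Same, either set | 12.9-16.3% |
| Adding the group main effect, either set | 13.7-18.6% |
| Interaction only, either set | 5.6-6.5% |
| Interaction required in both sets | 3.1-4.0% |
| Interaction significant before visit t-tests are read | 3.9-5.0% |
| Interaction only, intention-to-treat | 4.4-5.0% |

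The first five rows span roughly 7% to 19%.

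**5. What each ANOVA term measures.** The time term pools the arms. In the step 3 model with 15 per arm and identical arms, if both improve by 2 ISI points (assumed), it is significant in 74-98% of trials. The group term averages all three visits, including baseline, where randomization makes the expected difference zero. A true difference of 3.8 at both later visits would appear as (0 + 3.8 + 3.8) / 3 = 2.53. Only the interaction, or a between-group contrast at a post-baseline visit, addresses the hypothesis directly.

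**The case against.** The strongest reply is that a conventional reading produces no inflation: the interaction is tested first, and the t-tests follow as the post-hoc analyses. Under that order the error rate is 3.9-5.0%. This is a reasonable way to run the analysis, but the text does not prescribe it. The t-tests are named first and on an equal footing with the ANOVA, and post-hoc analyses are mentioned separately.

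A reader might infer from the list of tests that the trial's type I error simply is 12-15%. The document does not support that. The figure requires an any-test-wins rule, which is stated nowhere. It also requires visit-score t-tests, whereas the primary outcome is worded as changes. That part of the objection stands, and the figures here are conditional for that reason.

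A reader might also blame the two analysis sets. Running both is ordinary practice, and for the interaction alone the second set moves the error only from about 5% to 5.6-6.5%. Most of the inflation comes from having two visits and mixing t-tests with the ANOVA.

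Nor does the plan say that a significant time effect would count as success. The hypothesis is between-group, the t-tests are between groups, and the interaction is included. What the document does is label that term misleadingly.

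Finally, this is a condensed article, its Discussion calls the trial a pilot, and a primary visit or test hierarchy is often left to an analysis plan. Silence alone would be no finding. Here, though, the article states the tests, factors, sets and level, and states them unranked, alongside a sample size built for one test.

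**Conclusion.** The point holds as a badly fixed primary analysis, not as a demonstrated error rate. The Statistical method section provides several unranked routes to an ISI claim at P<0.05, against a design that allows for one.

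If any significant between-group result counted, the type I error would be about 9-10% (change-score t-tests at two visits, with or without the interaction), 12-15% (visit-score t-tests plus the interaction and group main effect), and roughly 7-19% across the wider assumptions on correlation, dropout and analysis sets. If one test in one set is decisive, it returns to about 5%. The sample size itself is not in dispute. The term labelled as treatment is change over time in both arms pooled and cannot support the hypothesis.

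**What to change.** Before unblinding, name one confirmatory between-group ISI test in the intention-to-treat set at two-sided 5%. Two choices would serve:

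- the baseline-adjusted group difference at one named post-baseline visit, reported with its 95% confidence interval, which is closest to the single comparison in the sample size; or
- the group-by-time interaction that is already specified.

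Make the other visit, the remaining tests and the per-protocol analysis supportive. Rename the within-patient factor as time. State that the time main effect, the group main effect (which averages in baseline) and within-group changes are not evidence of efficacy.

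The cost is a paragraph of wording, with no change to data collection or N. The small downside is that fewer results can be called confirmatory.
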